### Relevant concomitant care permitted or prohibited during the trial {11d}

As per hospital protocol (study setting), the care and interventions permitted will be used and no specific prohibited care is in this trial. As far as drug reactions are concerned, they will be treated by health care workers on the spot and will be reported afterwards.

### Provisions for post-trial care {30}

No post-trial care will be needed in our study setup as half-lives of the administered drugs are within hours to days.

### Outcomes {12}

Primary outcomes will include time to SARS-CoV-2 RT-PCR clearance, alleviation of symptoms, and better high-resolution computerized tomography (HRCT) chest score. Thirty-day mortality will be used as a secondary outcome. SARS-CoV-2 RT-PCR will be done on admission day (0 day) and then after every 4th day for 12 days or till the symptoms are resolved and RT-PCR gets negative. Symptom resolution is defined by the resumption of mild to moderate symptoms COVID-19 symptoms (defined by the definition of symptoms). RT-PCR will only be shown as positive or negative (as a limitation of our study of not getting the viral load). Time taken for the alleviation of symptoms will be measured as the number of days the patient remained symptomatic, i.e., the difference between onset of COVID-19 symptoms to complete resolution. HRCT chest scoring will be done as follows: Lungs divided into five lobes and each lobe is scored as 0 (no involvement), 1 (< 5% involvement), 2 (up to 25% involvement), 3 (26–49% involvement), 4 (50–75% involvement), and 5 (> 75% involvement). The overall HRCT chest score will be from 0 (no involvement) to 25 (maximum involvement) [16]. The HRCT findings are described via standard international terms, which are classified by the Fleischner Society glossary with peer-reviewed literature on viral pneumonia. The terms being used are ground glass opacity (GGO), crazy-paving pattern, and consolidation [17, 18]. Like a previous study [19], a maximum of 4 HRCT chest will be performed starting from day 0 followed by every fourth day till patients’ PCR become negative.

### Participant timeline {13}

Schedule of enrolment, interventions (including any run-ins and washouts), assessments, and visits for participants have been shown in a schematic diagram (Fig. 1).

**Fig. 1 Fig1:**
[figure not shown]
Participant timeline during study period

### Sample size {14}

Considering it a novel idea to use iodine in the management of COVID-19, no software was used to calculate the sample size (Fig. 2). However, arbitrarily 50 patients in each arm with a total of 200 patients sample size for a multi-centered study in Pakistan will be randomized. In this adaptive trial, sample size reestimation is planned to achieve the study objectives, if needed. Time taken for the elevation of the symptoms will be considered as relevant endpoint (RE) while SARS-CoV-2 RT-PCR clearance and HRCT chest score will be studied as additional endpoints (AE). The required sample size will be calculated with 0.05 alpha and 80% power of the study.

**Fig. 2 Fig2:**
[figure not shown]
CONSORT flow diagram

### Recruitment {15}

Recruitment will be done in Shaikh Zayed Medical Complex, Ali Clinic, and Doctors Lounge with mild to moderate symptomatic patients. All patients’ records will be analyzed at the center and eligible participants will be separated. All the eligible participants will be assessed according to our inclusion and exclusion criteria. Fully equipped site investigators with full precautions will do all these proceedings. At the start of the study trial, all recruited participants must provide a written informed consent form as per the plan to get them enrolled for the study.

## Assignment of interventions: allocation

### Sequence generation {16a}

Randomization will be done using lottery method. As patients might be admitted at different times so they will be recruited after taking written informed consent (following all standard protocol for infection control and disinfection) and will be randomized by selecting a slip from the box containing 50 slips of each arm labeled as A, B, C, and X. Arms A, B, and C will be the add-on interventional arms while arm X will be the placebo arm.

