### Trial design {8}

This is a placebo-controlled, multi-armed, add-on to standard therapy, interventional, randomized trial using a parallel group design. It is closed-labeled, adaptive with sample size reassessment, and multi-centered with a 1:1:1:1 allocation ratio design with a superiority framework.

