### Eligibility criteria {10}

All COVID-19 diagnosed and declared non-pregnant adults with mild to moderate illness will be recruited in the study. Patients with acute or chronic ailments, who are breastfeeding, or with history of iodine allergy will be excluded from the trial. Patients not giving consent will also be eliminated.

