### Concealment mechanism {16b}

The allocation sequence will be computer generated that will be concealed from site investigators, allocated participants, and treatment providers until the final interventional allocation is done. However, the sequence allocation will be conveyed telephonically to the respective investigator to allocate the patient in either group. Implementation of the intervention will be done by the help of co-investigators not involved in assessing clinical outcomes.

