### Methods for additional analyses (e.g. subgroup analyses) {20b}

Adjusted and subgroup analysis may be applied as per the biostatistician, if needed. In that case, both unadjusted and adjusted analyses are provided along with the main analysis.

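### Mild and moderate patients share one undivided draw and the primary analysis does not commit to using baseline severity; the draw is valid, but avoidable precision is lost

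*Protocol article*

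**What the plan says.** Eligibility criteria {10} admits both severity levels as one range: "All COVID-19 diagnosed and declared non-pregnant adults with mild to moderate illness will be recruited in the study". Trial design {8} describes the trial as "multi-centered with a 1:1:1:1 allocation ratio design with a superiority framework", and Sample size {14} sets "arbitrarily 50 patients in each arm with a total of 200 patients sample size".

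Sequence generation {16a} gives a lottery in which each patient "will be randomized by selecting a slip from the box containing 50 slips of each arm labeled as A, B, C, and X". Concealment mechanism {16b} says instead: "The allocation sequence will be computer generated". The two descriptions conflict, but neither names strata for severity or anything else.

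Table 1 under {20a} lists a multivariable Cox model for time to symptom alleviation (the RT-PCR clearance row shows no method of its own and appears to share it) and a mixed ordinal logistic model for HRCT score at day 4. No covariates are named. Section {20b} then says: "Adjusted and subgroup analysis may be applied as per the biostatistician, if needed". It adds that, in that case, adjusted and unadjusted results will accompany the main analysis.

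**The concern.** With 50 patients per arm, a single box can leave the arms visibly different in their share of moderate patients. All three iodine arms are compared with the same placebo arm, so an unlucky placebo arm moves all three comparisons in the same direction.

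Severity is plausibly prognostic for two of the three primary outcomes. The HRCT score measures extent of lung involvement and is analysed only four days after baseline, so it carries the baseline extent forward. Symptom duration runs from onset to complete resolution. An analysis that ignores a prognostic factor loses power, and in a Cox model it also pulls a real effect towards the null. The article puts adjustment outside the main analysis and leaves it to discretion, so this loss is not ruled out. At stake are power in a trial whose arm size was not derived, and the ranking of three formulations in small arms.

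**Working it through.** **Inputs from the protocol article.** Four arms of 50 slips, one box: 4 x 50 = 200, which reproduces the stated total. No effect size, event rate or SD is given, so there is no power figure to reproduce. Section {14} gives alpha and power only for the re-estimation: "The required sample size will be calculated with 0.05 alpha and 80% power of the study".

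**Assumptions (not in the documents).** Share moderate p = 30% to 50%. Severity hazard ratio for recovery, moderate v mild, 0.5 (range 0.7 to 0.35). Treatment hazard ratio 1.75 (above 1 means faster recovery). Mild placebo recovery rate 0.14 per day, daily assessment, 14-day horizon, two-sided 5%.

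**1. Size of chance imbalance.** For two arms of n = 50 drawn from N = 200, the SD of the difference in share moderate is sqrt[2p(1-p)/n x N/(N-1)].
- p = 0.3: sqrt(0.0084 x 200/199) = 9.2 points.
- p = 0.5: sqrt(0.0100 x 200/199) = 10.0 points.

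Simulating the box (200,000 draws):

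| Event | p = 30% | p = 50% |
|---|---|---|
| At least one iodine arm differs from placebo by 10 points or more | 64% | 70% |
| At least one iodine arm differs from placebo by 20 points or more | 9.7% | 14.3% |
| One given iodine-placebo pair differs by 20 points or more | 3.9% | 5.7% |

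Any two iodine-minus-placebo differences correlate at 0.50, because they share the placebo arm.

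**2. Type I error over all draws.** Under the single box with no treatment effect, the log-rank test ignoring severity rejects in about 5.2% of runs at severity hazard ratio 0.5. A continuous-outcome simulation (severity effect 0.5 or 1.0 SD, p = 50%) gives 5.1% and 4.7%. The draw does not inflate the error rate.

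**3. The conditional case.** If a split of 15/50 v 25/50 moderate has already occurred and there is no treatment effect, the mean log hazard ratio ignoring severity is about 0.146, and exp(0.146) = 1.16. Rejection is then about 7% to 9% across separate simulation runs, against about 5% to 6% with a severity-stratified test.

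**4. Power for one iodine-placebo comparison, severity ignored / severity-stratified log-rank.**

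| Severity hazard ratio | p = 30% | p = 50% |
|---|---|---|
| 0.7 | 74% / 75% | 73% / 74% |
| 0.5 | 68% / 72% | 65% / 70% |
| 0.35 | 60% / 69% | 55% / 67% |

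The gains are 1, 4 to 5, and 9 to 12 points. Simulation error is about one point, so the low end cannot be told apart from zero.

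**5. Where the gain comes from.** With the severity-stratified analysis held fixed (severity hazard ratio 0.5), the box and exact severity balance give 73% v 73% at p = 30% and 70% v 70% at p = 50%. Another run gave 71% v 73% and 71% v 70%. For a continuous outcome with adjustment, the figures are 69.3% v 70.3% (severity effect 0.5 SD) and 69.2% v 69.7% (1.0 SD). The gain comes from the analysis; changing the draw adds about 0 to 2 points.

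**The case against.** The strongest reply is that an unstratified draw is proper randomisation and that model covariates are normally fixed in the SAP, which is not shown. Table 1 already lists a multivariable Cox model, and {20b} promises both adjusted and unadjusted results if adjustment is used. An SAP could therefore name severity without contradicting the article.

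Much of this stands. The draw is valid, and the mere absence of a covariate list would be no finding. But {20b} is not silent: it makes adjustment discretionary and sets it beside the main analysis rather than in it. That is a stated choice, and a better one is available at almost no cost.

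Two practical objections also stand. Eligibility treats mild to moderate as a single range, and the article gives no rule dividing the two, so the class cannot be presumed to be recorded before allocation. Recruitment began on July 30, 2020, with completion estimated for February 15, 2022. Mortality is assessed 30 days after randomisation, so on those dates the last patient would be randomised by about January 16, 2022, three days before publication. Few allocations may remain to be stratified.

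A reader might infer from the conditional 7% to 9% that the lottery raises the false-positive rate. It does not: that figure presupposes a 20-point split, which any one pair reaches in about 4% to 6% of draws, and over all draws the rate stays near 5%.

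**Conclusion.** The point holds as a moderate weakness of efficiency and comparability. The stated primary comparisons do not commit to using baseline severity, although it plausibly affects symptom duration and HRCT score. With 30% to 50% moderate, a gap of 20 points or more between placebo and some iodine arm arises in about 10% to 14% of draws. Ignoring severity costs about 5 points of power at a severity hazard ratio of 0.5, and roughly 0 to 12 points across 0.7 to 0.35.

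The share moderate, the severity and treatment hazard ratios and the recovery rate are all assumptions; the documents give none of them.

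Two stronger readings are not supported. One is that severity drives all three primary outcomes: the article does not say so, and for RT-PCR clearance it is only an assumption. The other is that stratified randomisation would recover the lost power: nearly all the gain comes from the analysis.

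**What to change.** Before unblinding, amend {20a} and {20b} so that the primary analysis uses baseline severity for all 200 patients. Stratify the Cox models by baseline mild/moderate class. Adjust the HRCT model for that class and for the day-0 HRCT score, which is already collected. Report the unadjusted results as supportive.

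Reconcile the lottery in {16a} with the computer-generated sequence in {16b}. For any allocations still to be made, generate that sequence in concealed permuted blocks within the two severity strata. This mainly serves baseline comparability.

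Cost: a written mild/moderate definition, applied to baseline data for patients already randomised without knowledge of arm or outcome, and recorded before allocation for the rest; a second list for any remaining allocations; one analysis line; and a small amendment. No extra patients are needed.

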### Concealment mechanism {16b}

The allocation sequence will be computer generated that will be concealed from site investigators, allocated participants, and treatment providers until the final interventional allocation is done. However, the sequence allocation will be conveyed telephonically to the respective investigator to allocate the patient in either group. Implementation of the intervention will be done by the help of co-investigators not involved in assessing clinical outcomes.

### Implementation {16c}

The therapists will have no influential role in study outcomes and analysis while only disclosing the treatment plans to patients. Local site investigators and other study members that are involved in participant’s enrolment will not be allowed to receive allocation information to prevent study bias. Meanwhile, generation of allocation sequence and assignment of the intervention will be done by co-investigators.

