## Assignment of interventions: blinding

### Who will be blinded {17a}

Trial participants, care providers, outcome assessors, and data analysts are blinded, respectively, by using placebo group, by using site investigators to provide placebo or drugs to participants, by using blinded clinicians to assess the clinical outcome and laboratory or radiological findings, and by using analysts from other institution that are not having any conflict of interest in research. The details will be announced after locking the data in a database sheet at the end of the trial.

The study experimental drug and placebo will be prepared by the team of pharmacists and pharmacologists in the Department of Pharmacology and Toxicology, University of Veterinary and Animal Sciences, Lahore, Pakistan. Both drugs will look alike, as they will have same packing but unique randomization codes. Participants, site investigators, care providers, outcome assessors, study coordinators, data managers, and statisticians will be blinded, and blinding codes will be revealed at the end of this study.

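### The allocation call and the therapists' disclosure step conflict with the stated blinding and, followed literally, could unmask capsule arm A against placebo arm X

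*Protocol article*

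**What the plan says.** Four adjoining sections of the protocol article govern who knows what, and when.

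- **Sequence generation {16a}:** patients are randomized by "selecting a slip from the box containing 50 slips of each arm labeled as A, B, C, and X". The same section states that A, B and C are the active arms and X is placebo.
- **Concealment mechanism {16b}:** the sequence is "concealed from site investigators, allocated participants, and treatment providers until the final interventional allocation is done". It adds that "the sequence allocation will be conveyed telephonically to the respective investigator to allocate the patient in either group".
- **Implementation {16c}:** "The therapists will have no influential role in study outcomes and analysis while only disclosing the treatment plans to patients". The next sentence says that local site investigators and staff involved in enrolment "will not be allowed to receive allocation information to prevent study bias". Co-investigators generate the sequence and assign the intervention.
- **Who will be blinded {17a}:** the list covers patients, those who treat them, the investigators at the sites, those who assess outcomes and the coordinators of the study. It ends: "data managers, and statisticians will be blinded, and blinding codes will be revealed at the end of this study". The device is coded product: "Both drugs will look alike, as they will have same packing but unique randomization codes". On timing: "The details will be announced after locking the data in a database sheet at the end of the trial".

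Procedure for unblinding {17b} allows a participant's allocation to be revealed during the trial only when severe symptoms call for extra treatment, and any unblinding is to be reported.

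**The concern.** Two steps in the allocation sections pass on information that the blinding section says nobody at the site has. The first is a telephone call that gives an investigator the patient's group. The second is a conversation in which a therapist discloses the treatment plan to the patient. Neither is limited to a coded pack.

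Time to alleviation of symptoms is a primary outcome, and the Sample size section makes it the relevant endpoint for re-estimation. Symptoms are evaluated every day under Plans for assessment {18a}. If that evaluation relies even partly on what the patient says, a patient who knows the arm may report recovery differently, and a blinded assessor cannot undo that. RT-PCR clearance and HRCT score, the other primary outcomes, are less open to this.

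The point is separate from the difference in product form. Syrup and nasal spray are recognisable in any case. Arms A and X both take a capsule three times a day, so theirs is the comparison that coded, same-packed product could protect, and a disclosure step could undo that protection however well the capsules match.

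**Working it through.** No figure in the protocol article bears on this, so the check sets the sections side by side.

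1. **What the call conveys.** {16b} describes the content as the allocation of the patient to a group. It does not mention the randomization code that {17a} puts on the packs. {16a} states which letter is placebo, so whoever hears the letter knows whether the patient is on iodine.
2. **Who receives the call.** {16b} says the respective investigator. {16c} bars site investigators from allocation information and {17a} lists them as blinded. Co-investigators, who assign treatment under {16c}, could be meant, but {16b} does not say so.
3. **What the therapist discloses.** {16c} does not define treatment plans.
   - Reading (a), the regimen: how and when to take a coded product. This is compatible with {17a}.
   - Reading (b), the allocated treatment. This contradicts {17a} for participants and care providers. It is also an earlier reveal of a participant's arm outside the condition in {17b}.
   - The context leans toward (b) without settling it. The clause stands in the section on implementing the allocation, next to a sentence about allocation information. It protects against bias by keeping therapists away from outcomes and analysis, a safeguard that matters most for staff who know the arm.
4. **When concealment ends.** {16b} ends it at allocation, {17a} ends blinding at data lock. These are different things. Concealing the sequence until assignment is ordinary practice, and its end reveals nothing by itself. The conflict therefore rests on steps 1 to 3.
5. **Which comparison is exposed.** Under Interventions, A is a capsule, B a syrup, C a nasal spray, and the only placebo is an empty capsule. B and C can be told from X by form. A versus X is 50 + 50 = 100 of 200 patients.

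**Illustration only.** Suppose, with no support in the document, that there is no true effect, that disclosure occurs, and that it shifts the reported recovery hazard by a factor HR of 1.10 to 1.25. For one 1:1 comparison with d recoveries at two-sided 0.05, z = ln(HR) × √(d/4), and the rejection probability is Φ(z − 1.96) + Φ(−z − 1.96).

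| d | HR | z | Rejection |
|---|---|---|---|
| 100 (all recover) | 1.10 | 0.0953 × 5 = 0.477 | 7.6% |
| 100 | 1.25 | 0.2231 × 5 = 1.116 | 20.0% |
| 80 | 1.10 | 0.0953 × 4.472 = 0.426 | 7.1% |
| 80 | 1.25 | 0.2231 × 4.472 = 0.998 | 17.0% |

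The table shows what such a shift would do. It is no evidence that the shift will occur.

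**The case against.** The strongest defence is that the sections can be followed together. Co-investigators generate the sequence and assign treatment, the packs carry codes, and therapists explain how to take a coded capsule alongside standard care. {16c} nowhere says that therapists name active or placebo. The sentence after the disclosure clause bars enrolling staff from allocation information, {16b} keeps those who implement the intervention out of outcome assessment, {17a} provides blinded assessors, and {17b} restricts earlier reveals. Taken as a whole, the intention is plainly to blind.

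Most of this stands. A reader might infer that the protocol's own procedure reveals the arm to every patient in every arm from the first dose. The text does not support that: it needs reading (b) of an undefined term, and it treats the end of sequence concealment as if it were unblinding. The false-positive figures likewise rest on an assumed hazard shift and cannot be cited as the trial's error rate.

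The defence does not remove the wording of the call, which names a group rather than a code and a recipient who may be among those barred. Nor does it stop a site from reading the disclosure clause literally and believing that it complies. An intention to blind is a reason to align these sentences.

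**Conclusion.** The point holds as a conflict of wording with a practical consequence. {16b} and {16c}, followed literally, permit the arm to reach an investigator and the patient, while {17a} keeps both blinded to data lock and {17b} allows a participant's arm to be revealed earlier only for severe symptoms. It is not shown that any arm will be revealed.

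The avoidable exposure is the A versus X comparison on time to symptom alleviation. That assumes that capsules A and X otherwise match as {17a} says, and that daily symptom evaluation depends partly on patient report. The size of any bias cannot be derived from the document. The correction is worth making because it is nearly free and changes what sites do.

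**What to change.** - **{16b}:** state that the telephone call conveys only the randomization code of the pack to be dispensed, never the arm, and that arm identity stays masked to database lock. Say which role receives the call, consistent with the bar in {16c}.
- **{16c}:** replace the disclosure clause with: therapists explain how to take the coded product and neither know nor reveal the arm.
- **{17b}:** keep it as the only route by which a participant's arm is revealed before lock. The unblinded interim safety review in Interim analyses {21b} is a separate provision and is not affected.
- **{16a}:** if slips are drawn at the site, the letters on them need the same treatment, since X is identified as placebo.

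The cost is a few sentences of protocol text and a site instruction. {17a} already plans unique codes on the packs, so no extra patients are needed. Recruitment is reported as in progress, so the amendment should also record what sites have in fact been telephoning and telling patients.

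The change does not mask arms B and C, for which no placebo of matching form is described. Comparisons of B or C with X on symptoms should not be presented as blinded on the strength of it.
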